### 2.7. Treatment Outcome Measures

To measure the symptoms of inattention and hyperactivity–impulsivity, the Adult ADHD Self-Report Scale (ASRS v1.1) Symptom Checklist [66] will be used. The ASRS v1.1 is a scale developed to determine the presence and frequency of current ADHD symptoms in adults. The scale, which consists of 18 items, is rated by participants on a 5-point Likert scale ranging from 0 (*never*) to 4 (*very often*). The ASRS v1.1 yields two subscale scores, namely, inattention and hyperactivity–impulsivity.

The Adult Executive Functioning Inventory (ADEXI) [67] will be used to assess the executive functioning outcome in the present study. The ADEXI is a 14-item self-report scale assessing working memory and inhibition in adulthood with a 5-point Likert scale ranging from 1 (*definitely not true*) to 5 (*definitely true*). The ADEXI has a summed score ranging from 14 to 70. Higher scores indicate greater difficulty with executive functioning.

### 2.8. Sociodemographic Information and Clinical Characteristics

Sociodemographic information (e.g., gender, age, and ethnicity) and clinical characteristics (e.g., subtype of ADHD, comorbidity, date/year of first ADHD diagnosis, use of ADHD medication, and level of adherence to ADHD medication) will be collected for descriptive purposes.

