#### 2.1.2. Enhanced Treatment-as-Usual Control Group

Participants from the enhanced treatment-as-usual (eTAU) control group will receive the usual care that is provided to adults with ADHD across clinical settings in Malaysia, along with a 30 min online psychoeducation webinar on adult ADHD. The participants will be allowed to initiate, maintain, or discontinue a treatment as they wish. We play no role in determining the treatment plan of the participants. However, we will emphasize the importance of seeking treatment as needed from their respective clinicians throughout the trial. The participants will be required to report both pharmacological and non-pharmacological treatments that they have received through an online questionnaire during the trial period. Data from the eTAU control group participants receiving either mindfulness-based intervention or CBT from their treating clinicians during the trial period will be excluded from statistical analysis to avoid data contamination. The participants from the eTAU control group will receive an invitation to participate iMBI upon completion of data collection.

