### 2.3. Randomization

A simple randomization technique will be used to allocate eligible participants to either the iMBI treatment + TAU group or the eTAU control group. The present study will use sequentially numbered, opaque, sealed envelopes for randomization [61]. To ensure that the number of participants is balanced between both groups, even if the recruitment of participants ends earlier than expected, a permuted block of four and six will be used. To blind the participants regarding their conditions, they will be informed that they are going to receive an online healthcare program without providing information regarding their treatment condition.

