### 2.6. Inclusion and Exclusion Criteria

The six-item Adult ADHD Self-Report Screening Scale for DSM-5 [63] will be employed to identify prospective participants. With respect to the inclusion criteria, participants must have a diagnosis of ADHD established with the Diagnostic Interview for Anxiety, Mood, and Obsessive–Compulsive and Related Neuropsychiatric Disorders (DIAMOND)–ADHD Diagnostic Module [64], must be aged between 18 and 29 years old, and must be proficient in Mandarin. Participants taking psychotropic prescriptions will be allowed to participate if their prescriptions are stable for at least 6 weeks prior to their participation in the present study.

The exclusion criteria for the present study will include (1) history or current presence of nonalcohol and/or nontobacco substance dependence, psychotic illness, bipolar disorder, personality disorders, conduct disorder, chronic suicidal behavior, and self-injurious behavior as reported in the DIAMOND self-report screening questionnaire; (2) nonverbal intellectual ability of percentile rank 25 or below as described in Raven’s Progressive Matrices–Clinical Edition [65]; and (3) received CBT for ADHD or mindfulness training in the past 2 years.

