### 2.11. Data Analysis

Data will be analyzed by using the IBM Statistical Package for the Social Sciences (SPSS) version 27(IBM, Armonk, NY, USA). Multivariate analysis of covariance (MANCOVA) will be employed to assess mean differences of outcome variables at immediate post-intervention and 1-month follow-up between the two groups (i.e., iMBI + TAU vs. eTAU) simultaneously with baseline scores as covariates. Pairwise comparisons will be conducted to identify specific differences between the groups as deemed necessary. Statistical significance is set at *p* < 0.05. The magnitude of the effect size will be reported using Cohen’s *d* value. When necessary, study data will be analyzed using intention-to-treat analysis (ITT). For ITT, the last observation carried forward method will be used to impute missing values or dropouts. We will perform per-protocol analysis to examine the effectiveness of iMBI when implemented in an optimal manner.

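### ADHD medication status is recorded for description only, so nothing in the plan specifically addresses chance imbalance on it; adding entry status as a covariate is a cheap, modest gain in precision

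*Protocol article*

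**What the plan says.** Four parts of the protocol article bear on this.

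- **Role of the variable (2.8).** Among the clinical characteristics, "use of ADHD medication, and level of adherence to ADHD medication) will be collected for descriptive purposes". The section gives no time point for collection.
- **Analysis model (2.11).** Post-intervention and 1-month outcomes are compared by MANCOVA, "simultaneously with baseline scores as covariates". No other covariate is named.
- **Allocation (2.3).** "a permuted block of four and six will be used", and the stated aim is "To ensure that the number of participants is balanced between both groups". No stratification factor is named.
- **Who may enter (2.6).** Those on psychotropic prescriptions "will be allowed to participate if their prescriptions are stable for at least 6 weeks prior to their participation". Unmedicated participants are eligible too.

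Two further statements concern medication. Section 1.2.2 describes the efficacy of psychostimulants as well established, while citing nonadherence and intolerance. Section 2.1.2, written for the eTAU arm, says "The participants will be allowed to initiate, maintain, or discontinue a treatment as they wish" and requires treatments received during the trial to be reported.

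**The concern.** The trial mixes medicated and unmedicated participants, and the protocol itself treats stimulant medication as effective on the symptoms being measured. Status at entry may therefore predict follow-up inattention and hyperactivity-impulsivity beyond the baseline score. For example, users and non-users with the same score could follow different courses, because some users stop and some non-users start. The plan records the variable but assigns it a purely descriptive role, fixes the covariates as baseline scores, and blocks only for arm size.

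At about 50 per arm, a visible difference between arms in the share medicated would not be unusual. If one appears in the baseline table, the plan has no prespecified response, and that invites a post hoc adjusted analysis. What could be lost is some precision, together with a clean answer to a reader who asks about the imbalance.

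**Working it through.** **Inputs from the protocol article (2.5).** 45 per arm before attrition and 54 per arm enrolled. The plan states no figure on medication, so there is none to reproduce.

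**Assumptions (not in the documents).** Share medicated p: 10% to 50%. Residual effect of medication d, meaning the user versus non-user difference at follow-up after baseline adjustment, in residual SDs: 0.29 to 0.7.

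**Step 1. How likely is a chance imbalance?** The SD of the difference in the share medicated is sqrt(2p(1-p)/n). At p = 0.3 and n = 54 it is sqrt(2 × 0.3 × 0.7 / 54) = 0.088. Normal tail probabilities:

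| p | n per arm | SD | P(at least 10 points) | P(at least 15 points) |
|---|---|---|---|---|
| 0.1 | 54 | 0.058 | 8% | 1% |
| 0.2 | 54 | 0.077 | 19% | 5% |
| 0.3 | 54 | 0.088 | 26% | 9% |
| 0.5 | 54 | 0.096 | 30% | 12% |
| 0.3 | 45 | 0.097 | 30% | 12% |
| 0.5 | 45 | 0.105 | 34% | 16% |

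Exact binomial probabilities are within 2 percentage points of these.

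**Step 2. What does the baseline score already absorb?** Suppose medication shifts both baseline and follow-up by 0.5 SD, and the two scores correlate at 0.5 (assumed). Baseline adjustment leaves 0.5 × (1 - 0.5) = 0.25 SD, about half. In residual SDs (sqrt(1 - 0.5²) = 0.866) this is 0.25 / 0.866 = 0.29. A 10-point imbalance then moves the planned estimate by about 0.10 × 0.25 = 0.025 SD, against 0.05 SD with no baseline adjustment.

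If instead the effect beyond the baseline score is a full 0.5 residual SD, a 15-point imbalance moves the estimate by 0.15 × 0.5 = 0.075 SD. That is one eighth of d = 0.60. Section 2.5 states no single planning effect; 0.60 is what 45 per arm detects with 80% power at two-sided 5%.

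**Step 3. What would the covariate gain?** Relative effective sample size is (1 + p(1-p)d²) × 85/86 - 1. The first factor is the residual variance removed and the second is the lost degree of freedom, from about 86 at 45 per arm. At p = 0.5 and d = 0.5: 1.0625 × 0.988 - 1 = 5.0%.

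| Residual effect d | p = 0.1 | p = 0.3 | p = 0.5 |
|---|---|---|---|
| 0.29 | -0.4% | 0.6% | 0.9% |
| 0.5 | 1.1% | 4.0% | 5.0% |
| 0.7 | 3.2% | 9.0% | 10.9% |

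**Step 4. Validity and power by simulation.** 54 per arm, 6,000 runs per setting, a stable medication effect on both baseline and follow-up, correlation 0.5.

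- Type I error was 0.047 to 0.051 with baseline adjustment, with or without medication in the model. The mean estimate was unbiased in every model.
- With a true treatment effect of -0.5 SD and 30% medicated, power went from 0.829 to 0.833 for a medication effect of -0.5 SD, and from 0.829 to 0.840 for -0.8 SD.

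**The case against.** The strongest reply is that this is a choice, not an error. Adjusting for baseline outcome scores is standard. Randomisation balances medication in expectation, and chance imbalance is already allowed for in the standard error and the 5% error rate. All of that stands. A reader might infer from the descriptive role of medication that the comparison is unprotected or biased. The documents do not support that reading, and Step 4 contradicts it.

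It is also fair that section 2.6 requires prescriptions to be stable before entry, so a stable drug effect is already in the baseline scores. This stands in part: the scores absorb about half of such an effect under the assumptions of Step 2, and do not capture a later difference in course.

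The share medicated could be low. Section 2.10 recruits across campus channels, and section 2.6 establishes the diagnosis by the trial's own interview without asking for prior treatment. At 10% medicated the gain is negligible and can be slightly negative. This too stands and sets the lower end of the range.

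Two limits on the argument should be granted. Section 2.8 does not say that medication is recorded at baseline, although the stability criterion means that prescription status has to be known at entry. And the freedom to change treatment in section 2.1.2 concerns events after randomisation, which a baseline covariate does not correct. It bears on this point only as a reason why entry status may predict later change.

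The last objection is that further covariates are usually left to a fuller plan. Here, though, the article gives the variable a role and names the covariates, so the point is about stated choices.

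**Conclusion.** The point holds as a modest improvement in precision. No element of the plan specifically addresses chance imbalance in ADHD medication status, and differences of 10 points or more between arms would occur by chance in roughly 8% to 30% of trials with 54 per arm, for 10% to 50% medicated. There is no bias and no inflation of Type I error.

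The benefit of adjustment ranges from about zero (-0.4% to 1% effective sample size), where medication is uncommon or its effect is mostly in the baseline scores, to 4-5% at 30-50% medicated with a 0.5 SD residual effect, and at most about 11% at 0.7 SD. Share medicated, residual effect and baseline-to-follow-up correlation are all assumptions. The case for acting is that the change is nearly free and settles in advance how an imbalance will be handled.

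**What to change.** In section 2.11, prespecify ADHD medication use at entry (yes/no) as an additional covariate alongside the baseline scores in every group comparison. Amend section 2.8 so that this item is recorded at entry and is no longer described as purely descriptive; the other characteristics listed there can stay descriptive. State that medication changes after randomisation are not adjusted for, since they may themselves be affected by allocation.

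The cost is a sentence in each section and one degree of freedom of about 86. It should need no new data, because prescription status must already be known for the 6-week criterion in section 2.6. Running the permuted blocks separately for users and non-users is optional and not needed for the fix; if it is done, the factor should stay in the model.

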### 2.9. Ethical Considerations

The present study was approved by the Scientific Research Ethical Committee of Universiti Tunku Abdul Rahman (UTAR, Ref: U/SERC/93/2019). The present study was registered with ClinicalTrial.gov (NCT04229251). Information sheets and consent forms will be provided for all participants involved in the trial. We will discuss the trial with prospective participants regarding the information provided in the information sheets. Prospective participants will be able to have an informed discussion with us. Written consent from patients willing to participate in the trial will be obtained.

All study-related information will be stored securely at the study site. All participant information will be stored in double-locked file cabinets in areas with limited access. All questionnaires and data collection, process, and administrative forms will be identified by a coded ID number only to maintain participant confidentiality. All documents that contain names or any personal identifiable information, such as informed consent forms, will be stored separately from study records identified by code number. All local databases will be secured with password-protected access systems. Forms, lists, attendance lists, appointment books, and any other listings that link participant ID numbers to other identifying information will be stored in a separate locked file in an area with limited access. Participants’ study information will not be released outside of the study without the written permission of the participants.

### 2.10. Study Procedures

Recruitment of participants will take place in different ways. First, participants from the participating university will be randomly recruited. Second, participants will be recruited from the counselling center at the university. Third, participants will be recruited via campus-based online social media sites (e.g., Facebook) and students’ online portal of the participating university. Last but not least, recruitment presentations at the participating university will also be made to recruit participants. We will start to enroll participants in March 2021 by invitation. The trial is expected to begin in May 2021 and end in December 2021.

Interested individuals will receive a study information sheet and will be invited to a screening session to determine their eligibility. Written informed consent will be obtained from all participants. Eligibility of participants will be assessed using screening and diagnostic measures 2 weeks before the program starts. Data collection will be conducted at a designated laboratory. Participants will be required to complete all study measures. Outcome measures, including attention, hyperactivity, and executive functioning (working memory and inhibition), will be collected at baseline, immediate post-intervention, and 1-month follow-up. Figure 1 presents the Consolidated Standards of Reporting Trials (CONSORT) diagram of the present study.

### 2.11. Data Analysis

Data will be analyzed by using the IBM Statistical Package for the Social Sciences (SPSS) version 27(IBM, Armonk, NY, USA). Multivariate analysis of covariance (MANCOVA) will be employed to assess mean differences of outcome variables at immediate post-intervention and 1-month follow-up between the two groups (i.e., iMBI + TAU vs. eTAU) simultaneously with baseline scores as covariates. Pairwise comparisons will be conducted to identify specific differences between the groups as deemed necessary. Statistical significance is set at *p* < 0.05. The magnitude of the effect size will be reported using Cohen’s *d* value. When necessary, study data will be analyzed using intention-to-treat analysis (ITT). For ITT, the last observation carried forward method will be used to impute missing values or dropouts. We will perform per-protocol analysis to examine the effectiveness of iMBI when implemented in an optimal manner.

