### 2.2. Study Design

This is a single-blind randomized controlled trial. Participants who fulfil the inclusion and exclusion criteria will be randomly assigned to an 8-week online mindfulness-based intervention plus treatment-as-usual (TAU) group (i.e., iMBI + TAU) or an eTAU control group using a simple randomization technique. Inattention, hyperactivity–impulsivity, and executive functioning of the participants from both the iMBI treatment and eTAU control groups will be assessed at baseline (week 0), immediate post-intervention (week 8), and 1-month follow-up (week 12).

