### 2.5. Sample Size

Sample size estimation is based on a meta-analytic approach. This estimation includes mindfulness-based intervention studies of individuals with ADHD published from 2008 to 2019 [41,52,53,54,55]. Using a power of 80%, *α* = 0.05, and effect size *f* = ½ *d*, the sample size for the present study is estimated. For inattention, Cohen’s *d* ranges from 0.33 to 3.14. For hyperactivity–impulsivity, Cohen’s *d* ranges from 0.24 to 1.32. For executive functioning, Cohen’s *d* ranges from 1.08 to 2.16. For all treatment outcome variables, it is suggested that a sample size of 45 per condition is needed to detect a power of 0.80 and *α* = 0.05. The present study anticipates a 20% attrition rate, so a sample size of 54 participants per condition is needed, totaling 108 participants.

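### Section 2.11 leaves two routes for dropouts, deletion of recorded week-8 scores or LOCF; a repeated-measures model for each outcome as the main analysis avoids both

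*Protocol article*

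**What the plan says.** Outcomes "will be assessed at baseline (week 0), immediate post-intervention (week 8), and 1-month follow-up (week 12" (Protocol article, section 2.2). Section 2.11 names one inferential procedure, a MANCOVA "to assess mean differences of outcome variables at immediate post-intervention and 1-month follow-up between the two groups", "simultaneously with baseline scores as covariates".

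Missing data come two sentences later and are conditional: "When necessary, study data will be analyzed using intention-to-treat analysis (ITT"). Imputation belongs to that analysis: "For ITT, the last observation carried forward method will be used to impute missing values or dropouts". A per-protocol analysis is also planned: "We will perform per-protocol analysis to examine the effectiveness of iMBI when implemented in an optimal manner". The section does not say which of these is the main analysis, or what makes the intention-to-treat analysis necessary.

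Section 2.5 shows that loss is expected: "The present study anticipates a 20% attrition rate".

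**The concern.** A MANCOVA needs a complete vector of outcomes and covariates for each person. If weeks 8 and 12 enter one model without imputation, a participant who attends at week 8 but not at week 12 is removed altogether. The week-8 comparison then rests on people selected by something that happens four weeks later.

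Precision is lost even when dropout is random. If people who did not improve are less likely to return, and this pattern differs between arms, the week-8 effect is biased as well. The one remedy that the text offers, LOCF, keeps everyone but gives those lost before week 8 their baseline score as their outcome. So neither route makes good use of the data at the visit with the most observations.

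**Working it through.** **Inputs from the protocol article.** 45 per arm raised to 54 for 20% attrition (section 2.5); visits at weeks 0, 8 and 12 (section 2.2); significance level 0.05 (section 2.11), taken as two-sided.

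**Assumptions not in the document.** How the 20% splits before and after week 8; a true effect of 0.60 SD at both visits; correlation 0.5 between baseline and each later score, and 0.7 between weeks 8 and 12.

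**Step 1: the plan's own figure.** 45 × 1.20 = 54 reproduces the enrolled number. The 45 cannot be derived, because section 2.5 gives only ranges of Cohen's *d*. Working back, a two-sample t-test with 80% power needs 44.6 per arm at *d* = 0.60, so 0.60 is used here. After 20% loss, 54 × 0.80 = 43.2 per arm are complete at both visits.

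**Step 2: precision under random loss.** Let w be the fraction lost by week 8. Then n8 = 54 × (1 − w) per arm have week-8 scores, and the joint complete-case model uses 43.2. The standard error ratio is √(n8 / 43.2). With equal random loss before week 8, LOCF gives an expected week-8 effect of (1 − w) × 0.60, because the carried-forward baselines contain no arm difference.

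| Lost by week 8 | n8 per arm | Week-8 records deleted, both arms | SE ratio | Power at 0.60, unadjusted: all week-8 scores vs complete cases | LOCF effect at week 8 |
|---|---|---|---|---|---|
| 0% | 54.0 | 21.6 | 1.118 | 0.871 vs 0.787 | 0.60 |
| 5% | 51.3 | 16.2 | 1.090 | 0.853 vs 0.787 | 0.57 |
| 10% | 48.6 | 10.8 | 1.061 | 0.833 vs 0.787 | 0.54 |
| 15% | 45.9 | 5.4 | 1.031 | 0.812 vs 0.787 | 0.51 |
| 20% | 43.2 | 0 | 1.000 | 0.787 vs 0.787 | 0.48 |

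With baseline adjustment and 10% lost by week 8, simulated power falls from 91.5% to 88.4%.

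**Step 3: bias.** Simulations used 54 per arm, 10% random loss before week 8 and about 11.1% of the remainder afterwards (0.90 × 0.889 = 0.80 retained). The quantity is the baseline-adjusted week-8 effect for one outcome, with a true value of 0.60.

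- Random later loss (4,000 replicates): 0.601 from complete cases and 0.601 from all week-8 scores; standard errors 0.184 and 0.176.
- Later loss related to outcome in the same way in both arms: 0.599 against 0.601, so no material bias.
- Later loss of non-improvers in the iMBI arm only, log-odds 1 or 2 per SD of change (6,000 replicates): 0.675 or 0.720 from complete cases, against 0.599 or 0.601 from all week-8 scores. With no true effect, rejection is 7.6% or 11.6%, against 5.4% or 5.3%. A 4,000-replicate repeat gave 0.68 and 0.72, with rejection of 7.0% and 9.2%.
- A different arm-specific pattern (log-odds 1.5 per SD of the week-8 score in iMBI, flat 6% in control): 0.748 against 0.601.
- LOCF at week 8 gave about 0.54 under random, same-in-both-arms and this last arm-specific loss.

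**The case against.** The strongest reply is that the deletion problem needs two contestable readings at once. First, *simultaneously* may mean that the several outcomes are analysed together at each visit. There would then be one MANCOVA per visit, and no week-8 score would depend on week-12 attendance. Second, *when necessary* may simply mean whenever there is dropout. LOCF would then fill the outcome vector before the MANCOVA and nobody would be deleted. The article never calls the analysis complete-case. Both replies stand: deletion is one fair reading, not the stated plan.

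The bias scenario can also be called severe. Log-odds of 1 to 2 per SD are odds ratios of about 2.7 to 7.4, acting in one arm only, and the protocol has no data showing such a pattern. That stands too. One-sided loss is not fanciful, since only the iMBI arm has eight weekly sessions and home practice (section 2.1.1) while the control arm has a single webinar (section 2.1.2), but it remains an assumption. In addition, the simulated rejection rates belong to a single-outcome week-8 contrast and not to the multivariate test.

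Finally, a journal article leaves detail to the full protocol or analysis plan. That carries less weight here, because section 2.11 does fix the model, the visits, the covariates and the imputation method. The objection is to those choices. Reading the text the other way does not rescue it either: it leads to LOCF, with the shrinkage shown above.

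**Conclusion.** The point holds in conditional form. Section 2.11 permits a joint MANCOVA without imputation, which would discard recorded week-8 scores, and its stated alternative is LOCF. With 20% total loss and half of it after week 8, the first route deletes about 11 week-8 records (97.2 − 86.4) and raises the week-8 standard error by about 6%, or 0 to 12% across splits. The second pulls a true 0.60 to about 0.54.

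A reader might go further and infer that the main analysis is a complete-case analysis, that it overstates the effect, and that it exceeds the 5% error rate. The document does not support that. It names no main analysis set and allows the other readings above. Bias from deletion also requires later loss that relates to outcome differently in the two arms. Under assumed iMBI-only loss of non-improvers, 0.60 is estimated as 0.68 to 0.72; under the same mechanism in both arms there is no material bias; and under LOCF the error runs towards zero in the scenarios examined. This is a worthwhile, inexpensive improvement and not a demonstrated invalidity.

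**What to change.** In section 2.11, make the analysis of all participants as randomised the main analysis and remove the condition attached to it. For each outcome, fit a linear mixed model for repeated measures with arm, visit, arm-by-visit, baseline score and baseline-by-visit, and an unstructured covariance. Include everyone with at least one post-baseline score, and report the arm difference at week 8 and at week 12 separately. LOCF is then not needed for the main result. The model assumes that loss is explained by the recorded scores, and the text should say so.

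Keep any MANCOVA as a secondary analysis run separately at each visit, so that week-8 scores are never dropped because of week-12 absence.

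The cost is a change of wording and a different procedure (MIXED) in the same SPSS package, with no new data, visits or participants. The downside is that the single omnibus multivariate p-value is no longer the headline result.

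### ITT is made conditional with no trigger, per-protocol is firm and no primary population is named, so the headline population could be chosen after the data are seen

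*Protocol article*

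**What the plan says.** Section 2.11 (Data Analysis) is the only place that sets out analysis populations.

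- **Main model.** A MANCOVA with baseline scores as covariates "will be employed to assess mean differences of outcome variables at immediate post-intervention and 1-month follow-up between the two groups". No population is attached to it.
- **ITT.** "When necessary, study data will be analyzed using intention-to-treat analysis (ITT"). No condition is given for when it becomes necessary.
- **Missing data.** "For ITT, the last observation carried forward method will be used to impute missing values or dropouts". No handling of missing values is given for any other analysis.
- **Per-protocol.** "We will perform per-protocol analysis to examine the effectiveness of iMBI when implemented in an optimal manner". This is unconditional, and the article does not define the set.

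Section 2.1.2 adds a rule for the control arm: data from eTAU participants who receive a mindfulness-based intervention or CBT from their clinicians "during the trial period will be excluded from statistical analysis to avoid data contamination". No matching rule is stated for the iMBI arm.

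Section 2.5 gives the planning figures: "a sample size of 45 per condition is needed to detect a power of 0.80", "The present study anticipates a 20% attrition rate", "so a sample size of 54 participants per condition is needed, totaling 108 participants".

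**The concern.** The comparison that randomisation protects is the one that keeps everyone in the arm assigned. Here that analysis is optional, the analysis that selects on behaviour after randomisation is firm, and neither is called primary. With significance at 0.05 as the only stated criterion, nothing in the text prevents the team from deciding, with the results in view, whether ITT was needed and which population carries the conclusion.

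The stated objective (section 1.2.5) is the effectiveness of iMBI, and the conclusions are meant to inform practitioners. That calls for the effect of being offered the programme. Sets defined by completion, adherence or outside treatment can differ between arms in ways unrelated to the programme's effect. The article lists vigilance and planning among the prominent deficits in ADHD (section 1.2.1), so a link between adherence and outcome is plausible, though not established.

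**Working it through.** **1. The plan's own sample size.** Inputs from section 2.5: 45 evaluable per arm, 20% attrition. 45 × 1.20 = 54 per arm and 2 × 54 = 108, which reproduces the stated figures.

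**2. How many participants the ITT decision moves.**
- Lost at 20%: 108 × 0.20 = 21.6, about 22.
- Remaining: 108 × 0.80 = 86.4 in total; 54 × 0.80 = 43.2 per arm.

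This takes the 20% as the share lacking a value that the model needs. A MANCOVA without imputation drops anyone missing any modelled outcome or covariate. The count would be smaller for a model of week 8 alone if some participants leave only later, and larger with scattered missing values. Exclusions under section 2.1.2 come on top; the article gives no figure for them.

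**3. The rules side by side.**

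| Rule | Status | Effect on who is analysed |
|---|---|---|
| MANCOVA (2.11) | firm | no population named; complete data needed unless imputed |
| ITT with LOCF (2.11) | conditional, no trigger | restores those with missing data |
| Per-protocol (2.11) | firm, set undefined | removes non-adherers, however defined |
| Outside MBI or CBT (2.1.2) | firm, controls only | removes randomised controls by later treatment |

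The last rule conflicts with ITT even if ITT is carried out.

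**4. What a free choice could do (illustration, no true effect).** Simulation: 54 per arm, one outcome, ANCOVA on baseline, about 20% dropout, 6,000 runs for each setting. The baseline–outcome correlation was assumed to be 0.3, 0.5 or 0.7. Entries are the rejection rate at nominal 0.05 for each correlation in turn.

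| Dropout (assumed) | Completers | LOCF | Smaller p of the two |
|---|---|---|---|
| Random, both arms | 0.049, 0.051, 0.052 | 0.047, 0.053, 0.053 | 0.063, 0.064, 0.061 |
| iMBI non-improvers leave more often | 0.079, 0.088, 0.092 | 0.111, 0.112, 0.102 | 0.122, 0.121, 0.110 |

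In the second row, dropout in the iMBI arm rises with worse change and averages about 20%; in controls it is a flat 20%. The Monte Carlo standard error near 0.05 is √(0.05 × 0.95 / 6000) ≈ 0.003. The simulation includes neither a per-protocol set nor the section 2.1.2 exclusion.

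**5. Selection on adherence (illustration).** Suppose the least adherent fraction q of one arm is removed and adherence correlates 0.3 with the outcome residual (assumed). The shift in that arm's mean is 0.3 × φ(z)/(1 − q), with z the q-quantile of the standard normal.
- q = 0.20: 0.3 × 0.35 ≈ 0.10 residual SD.
- q = 0.30: 0.3 × 0.50 = 0.15 residual SD.

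The result is proportional to the assumed correlation, for which the article gives no value.

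**The case against.** The best defence is that the sentence after the ITT sentence speaks of imputing missing values or dropouts, so the condition can be read as applying whenever data are missing. With 20% attrition expected, ITT would then be carried out. Detailed definitions of analysis sets are also commonly left to a SAP, which is not shown.

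Part of this stands. The article nowhere says that the default is a completers' analysis. A reader might infer that it does; this is a strong inference from tying imputation to ITT alone, but it is not stated text. The defence does not remove the problem. On the generous reading there is still no primary population, the control-arm exclusion still applies and per-protocol still stands beside ITT without rank. Nor is this a detail left to a SAP: the article states a rule, and the rule makes ITT optional.

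Other stronger readings are tempting and not supported:

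- **Selection acts in the iMBI arm only.** Section 2.1.2 removes controls as well, and the per-protocol set is undefined, so no adherence threshold can be attributed to the plan.
- **Completer and per-protocol results must favour iMBI.** Baseline scores are covariates, so selection on baseline severity is at least partly adjusted. Attrition is planned for both arms, and under random dropout the completers' analysis held its level at about 0.05. The direction of bias is not established.
- **Using the word effectiveness for the per-protocol result is a causal error.** The sentence is qualified as applying to optimal implementation and does not claim primary status.
- **A complier-average analysis is required.** It is an optional extra that needs its own assumptions.

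**Conclusion.** The point holds as a defect in how section 2.11 fixes the analysis population, made worse by the exclusion in section 2.1.2. It rests on the wording: ITT is conditional with no trigger, per-protocol is firm, no population is primary, and imputation belongs to ITT alone. It matters because it determines the headline result, and it has to be settled before outcome data are seen.

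The one size that follows from the plan's own figures is about 22 of 108 randomised participants whose inclusion may depend on the undefined decision. The rest is illustrative. Choosing the smaller p of completers and LOCF raises the type I error to about 0.061–0.064 under random dropout, and to about 0.11–0.12 if iMBI non-improvers leave more often. The shift of 0.10–0.15 SD is correct arithmetic on an assumed correlation of 0.3. None of these is an estimate of bias in this trial.

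**What to change.** In section 2.11, replace the conditional ITT sentence with a firm one, for example: *The primary analysis includes all randomised participants in the arm to which they were assigned, regardless of sessions completed or other treatment received during the trial.* Then:

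- label the per-protocol analysis as supportive only;
- in section 2.1.2, move the exclusion of controls who receive mindfulness-based treatment or CBT to a supportive or sensitivity analysis. If it stays as written, it contradicts the new sentence.

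This settles the population, not the missing-data problem. In the assumed informative-dropout scenario, LOCF rejected more often (about 0.10–0.11) than completers (about 0.08–0.09), so the handling of missing outcomes needs its own justification.

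The cost is a few sentences across two sections, carried into any SAP. The primary estimate may be less favourable than a per-protocol one.
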